### Interventions and CTA protocol

Both laparoscopic and robotic gastrectomy procedures associated with the standard extent of lymph node dissection were performed by reference to the 2018 version of Japanese Gastric Cancer Treatment Guidelines [9], and the resection range of the stomach, which is based on the Japanese Gastric Cancer Association classification [17], is according to lesion location and size, which is described in gastroscopy reports. Although there are three classic types of digestive tract reconstruction named after Billroth I, Billroth II and Roux-en-Y, the last type was recommended in this study. The TNM staging system was adopted from the eighth version of the American Joint Committee on Cancer (AJCC). Perioperative management will follow the basic principles of enhanced recovery after surgery in both groups. Chemotherapy guidance and follow-up will be conducted for patients with non-early gastric cancer based on 2021 version of NCCN gastric cancer clinical practice guidelines in oncology [18]. This study does not make uniform mandatory requirements for chemotherapy regimens and cycles, but postoperative adjuvant chemotherapy needs to be recorded in the CRF table. This study does not recommend routine postoperative adjuvant radiotherapy. Analgesic and antiemetic drugs are allowed in treatment measures, and the side effects of drug treatment should be recorded in the CRF.

A preoperative mandatory abdominal enhanced CT scan will be performed in both the experimental group and the control group to evaluate the clinical stage of the tumour. Moreover, compared with the non-CTA group, the patients in the CTA group will be asked to undergo the CTA examination once they are randomly assigned to the experimental group. To improve adherence to the intervention protocols, the patients will be fully informed of the potential short-term clinical recovery course and long-term oncological effects. Regular research meetings are held to provide relevant study guidance for researchers. For the researchers, there are mainly three ways to enhance adherence to intervention protocols including researcher training, regular researcher meetings and regular visits to the sub-centres. Abdominal enhanced CT will be performed using a 64-detector row CT scanner in this study, while the type of CT equipment is according to what is available in each participating centre. The procedure of the abdominal enhanced CT was set to ensure the same standard for the reconstruction of the perigastric arteries across centres. Fasting no less than 8 h before the examination is required, and an injection of 10 mg anisodamine 10 min before the examination is necessary for the purpose of reducing gastric distention and motility. Nonionic iodinated contrast material will be used as the contrast agent, injected at a speed of 4.0 ml/s by an automatic injector, and its volume is based on the weight of the patient; for example, for patients weighing 60 kg or less, the lower limit is 120 ml, and for patients weighing more than 75 kg, the upper limit is 150 ml.

### For qualification of the surgeons

To ensure the quality of the clinical trial and guarantee the safety of patients, some essential principles should be achieved before a surgeon participates in the study. Apart from the surgeon performing at least 100 laparoscopic or robotic gastrectomies, which means that the learning curve has been completed, two surgical videos are needed to be submitted to a surgical treatment quality control committee that consisted of two senior surgeons independent of the trial to verify that the surgeon meets the research requirements.

### For the quality of the CTA image

The scanning range of the abdominal enhanced CT will be the upper abdomen, from the top of the diaphragm to the level of the inferior mesenteric artery, and the region of interest (ROI) is at the level of the celiac artery. Since the quality of CTA is of utmost importance in this trial, we set up criteria to ensure the image quality: (1) there was no bundle sclerosis artefact produced by metal foreign bodies in vitro, which obviously affected the display effect of the arteries; (2) there was no motion artefact caused by motion displacement; and (3) MPR, VR, MIP and other three-dimensional reconstruction techniques could display the perigastric artery clearly. After the reconstruction of the CTA, the anatomy of the perigastric arteries will be captured to evaluate their origins and branches, such as the celiac artery and the hepatic artery, by two senior radiological specialists. In addition, to decrease potential damage to the perigastric arteries, the surgeon and the surgical team should have a good acquaintance with the anatomy of the perigastric arteries and the perigastric artery types, which were divided into seven types based on our previous proposal for a novel classification of the perigastric arteries, which is recorded in the CRF.

### Adverse events

Adverse events are defined as unfavourable and negative clinical outcomes occurring when patients receive medical care. Any adverse events associated with the CTA and the surgery will be recorded and treated properly. Nonionic iodinated contrast material will be used in this trial, and serious allergic reactions, including hypotension, dyspnoea and anaphylactic shock, have not been observed for this contrast agent. If an allergic reaction does occur, withdrawal of the enhanced CT examination from the patient will be documented as an adverse event. Meanwhile, patients can withdraw from the clinical trial without any responsibility. All participants were guaranteed by the national medical security system in the event of suffering any unpredictable injury during the trial. To monitor the enrolled data and ensure the safety, effectiveness and integrity of this clinical trial, an independent data and safety monitoring committee (DSMC) that consists of two senior surgeons, one statistician and one medical ethics expert was set up. The DSMC will evaluate the progression of patient enrolment and make suggestions to the sponsor regarding whether to continue the trial as planned, continue after modifying the protocol or suspend or terminate the trial.

### Postoperative care

The patients will be assessed by the doctor in charge twice a day, and any discomfort or surgical complications should be appropriately explained and handled; moreover, this management will be recorded in the CRF. The patients should be discharged from the hospital when they meet these criteria: postoperative pain is well controlled with or without oral analgesics, the body temperature is no more than 37 °C, the postoperative complications are well managed, oral semiliquid food is tolerated and the patient can sustain daily walking activity.

### Follow-up

A specified follow-up team will be arranged for the patient after surgery at each participating centre, and the main follow-up methods include outpatient visits, telephone visits or mail visits. The postoperative recovery course, which includes a short-term recovery course and the long-term oncological effects and adjuvant therapy, will be assessed, as shown in Fig. 2. For the first year after surgery, the patient needs to be reviewed every three months. For the next 2–3 years, the patient needs to be reviewed every 6 months. The follow-up programme includes a physical examination, laboratory tests that consist of routine blood tests, liver and kidney function tests, electrolytes, and digestive tract tumour markers (including the examination of CEA, CA125, CA199 and CA724). Moreover, gastroscopy and chest and abdominal CT will be performed once a year and every 6 months, respectively. MRI or PET-CT will be used when a tumour recurrence or metastasis is suspected. In addition, the survival status of the patients will be noted in the CRF, and patients who undergo a follow-up of 36 months are essential for the study.

**Fig. 2 Fig2:**
[figure not shown]
The items of enrolment, interventions and assessments in the flowchart. The symbol of × represent that the program needs to be collected. −1, 2 weeks before operation; 0, perioperation; 1, postoperative adjuvant chemotherapy time; follow-up 2~10 refers to time points that listed in the following: 2, 1 months after surgery; 3, 3 months after surgery; 4, 6 months after surgery; 5, 9 months after surgery; 6, 12 months after surgery; 7, 18 months after surgery; 8, 24 months after surgery; 9, 30 months after surgery; 10, 36 months after surgery

### Data collection and analysis

An a priori designed and coincident case report form (CRF) will be used to record the information required by the study, such as baseline characteristics, laboratory data, perioperative clinical recovery course and long-term oncological outcomes, and a designated clinical investigator is responsible for the collection of data at each centre. Moreover, to keep track of changes to the data, any correction to the raw data requires signing the date and the investigator’s name. A monthly data check that includes data summarized by each centre, abnormal data and delayed data in progress tracking is required during the trial period.

Continuous variables will be presented as the mean ± standard deviation, while classification variables will be described as numbers (*N*) and percentages (%) to express the difference between two groups. To compare continuous variables for the two groups, Student’s *t* tests or Mann–Whitney *U* tests will be performed, and categorical variables will use the *χ*^2^ test or Fisher’s exact test. OS and DFS, defined as the time from surgery to death and the time from surgery to tumour recurrence or death from any cause, respectively, will be assessed by the Kaplan–Meier method with the log-rank test to analyse the differences in the survival curves. A Cox proportional hazards regression model with a 95% confidence interval will be used to perform univariate and multivariate analyses. Subgroup analyses will also be performed, with participants stratified by BMI (25.0 to 29.9 kg/m^2^, ≥ 30 kg/m^2^), to verify the effect of CTA on short-term and long-term clinical outcomes in overweight and obesity patients between CTA group and non-CTA group. For missing data, multiple imputation was used to obtain complete datasets. A *P* value less than 0.05 will be considered statistically significant. The 25th version of SPSS (SPSS Inc., Chicago, IL, USA) will be used to analyse the data.

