### Inclusion and exclusion criteria

The inclusion criteria are as follows: (1) patients with a pathological diagnosis of gastric adenocarcinoma by gastroscopy, (2) patients aged between 18 and 75 years old, (3) patients with a body mass index (BMI) not less than 25.0 kg/m^2^, (4) tumour clinical stage evaluated by CT imaging (T1~T4a, N0~3, M0), (5) patients with an Eastern Cooperative Oncology Group (ECOG) score 0–1 points, (6) the surgical approach is laparoscopic or robotic surgery, and (7) patients who are willing to participate in the study and sign the informed consent form.

The exclusion criteria are as follows: (1) patients whose tumour clinical stage conformed to T4b or M1 and whose tumour was found to be unresectable during the operation; (2) patients who suffered from a history of other malignant tumours or tumours of low malignant potential (such as giant cell tumours of the bone, pseudomyxadenoma of the appendix, invasive fibroma); (3) patients who have other serious systemic diseases and could not tolerate the trauma of surgery; (4) patients with non-adenocarcinoma-type malignant tumours verified by pathology after surgery; (5) patients with residual gastric cancer; (6) patients who are allergic to iodine contrast agents; (7) patients who received neoadjuvant therapy before surgery; (8) pregnant or lactating patients; and (9) patients who are participating in other clinical trials.

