### Randomization

In this trial, eligible patients will be randomly assigned to either the CTA group or the non-CTA group in a 1:1 ratio. A central dynamic, stratified strategy was adopted for the aim of randomization. The sequence of randomization was generated by a certain doctor who was independent of this trial using the method of Pocock-Simon minimization by SAS 9.3 (SAS Institute Inc., Cary, NC, USA) and stratified by participating site (14 hospitals) and surgical approach (laparoscopic or robotic). The above information provided by the participating centres was submitted to the data centre at the Department of Gastrointestinal Surgery, Affiliated Hospital of Qingdao University, China, where central randomization was executed. Consequently, the allocation information will then be sent to each participating site. The allocation procedure was not blinded to the investigators or patients but was masked for data collection and analysis.

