## Discussion

Minimally invasive surgery, such as laparoscopic and robotic techniques, has gained great popularity due to its minimal trauma in the treatment of gastric cancer in recent decades [3, 19–21]. However, laparoscopic surgery lacks three-dimensional anatomical vision and distinguishes the relationship between intra-abdominal organs and vessels in spatial conformation compared with open surgery. Meanwhile, the local magnifying effect of laparoscopy makes it easy for the surgeon to lose their overall judgement of the adjacent relationship of perigastric tissues, and it is difficult to dissect the celiac artery and its branches accurately.

CT angiography (CTA), which is noninvasive and easy to perform, is a combination of CT enhancement technology and thin-layer, large-scale, fast scanning technology [22]. It can clearly show the details of blood vessels in all parts of the body through reasonable postprocessing of reconstruction. It is of great value for vascular variations and vascular diseases and displays the relationship between lesions and vessels [14, 23]. Through this technology, we can clearly understand the anatomical conditions of gastric blood vessels and related blood vessels and provide better and more detailed lesion information for planning gastric cancer surgery.

The possibility of unanticipated bleeding may be increased in the process of lymph node dissection among obese patients underwent laparoscopic or robotic gastrectomy. However, under the application of CTA, unpredictable perigastric artery damage and intraoperative bleeding, especially for the celiac trunk and its three major branches (left gastric artery, splenic artery and common hepatic artery), could be reduced during lymph node dissection with perigastric arteries navigation. Natsume et al. demonstrated that the visualization of the precise anatomy around the gastric with the application of dual-phase 3D CT is useful and essential modality, which may contribute to assist surgeons to reduce the intraoperative blood loss during laparoscopic gastrectomy [24]. Shen et al., who proposed a novel perigastric arteries classification, showed that compared with patients with non-high risk type vascular variation, patients with high risk type vascular variation have a high incidence of potential intraoperative vascular injury during laparoscopic radical gastrectomy [15].

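### Blood loss is compared without baseline covariates although BMI and clinical stage are known at eligibility: a loss of precision of unknown size, not bias

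*Protocol article*

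**What the plan says.** Under Data collection and analysis, the article deals with all continuous outcomes in one sentence. It opens "To compare continuous variables for the two groups" and continues "Student’s *t* tests or Mann–Whitney *U* tests will be performed". Neither test takes covariates. Blood loss is the primary endpoint (Outcomes); lymph node count, length of stay and cost are the other main continuous outcomes. The only regression named comes after the definitions of OS and DFS: "A Cox proportional hazards regression model with a 95% confidence interval will be used to perform univariate and multivariate analyses". A Cox model does not serve a volume in millilitres. BMI enters the analysis only as a subgroup split at 30 kg/m², which does not adjust the overall comparison.

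Under Randomization, allocation was generated "using the method of Pocock-Simon minimization by SAS 9.3" and "stratified by participating site (14 hospitals) and surgical approach (laparoscopic or robotic"). BMI and stage are not balancing factors.

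Three passages bear on possible covariates:

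- The Discussion says: "The possibility of unanticipated bleeding may be increased in the process of lymph node dissection among obese patients" having laparoscopic or robotic surgery.
- Inclusion criterion 3 is a minimum BMI, and criterion 4 is "tumour clinical stage evaluated by CT imaging (T1~T4a, N0~3, M0"). Both are therefore known at eligibility.
- Under Interventions and CTA protocol, the resection range "is according to lesion location and size, which is described in gastroscopy reports".

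**The concern.** The authors themselves expect bleeding to vary with body size, and they hold BMI for every patient before allocation. An unadjusted test leaves that variation in the error term. The planned difference is 21 ml against standard deviations of 66.4 and 88.4 ml, and the trial is sized to reach 80% power with almost no reserve, so any precision recovered from existing data is worth having.

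Timing matters too. If adjustment is not pre-specified and an imbalance shows up later, adjusting for it then is post hoc and open to challenge, more so in a trial whose investigators know the allocation.

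**Working it through.** **Inputs** (Sample size computation): means 72.5 and 93.5 ml, SDs 66.4 and 88.4 ml, one-sided α = 0.05, power 80%, dropout about 10%, 191 per arm.

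**1. Reproduce the plan's figure.**
- Difference = 93.5 − 72.5 = 21.0 ml.
- Average SD = √((66.4² + 88.4²)/2) = 78.18 ml.
- n per arm = 2 × 78.18² × (1.645 + 0.842)² / 21² = 172 after rounding up.
- With dropout, 172/0.90 = 191.1, which agrees with the stated 191.

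The stated size is thus that of an unadjusted one-sided comparison.

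**2. Unadjusted precision and power at 172 evaluable per arm.**
- SE = √((66.4² + 88.4²)/172) = 8.43 ml.
- Power = Φ(21/8.43 − 1.645) = Φ(0.846) = 80.1%.

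**3. With baseline covariates.** If they explain a share R² of the blood-loss variance (taken as equal in both arms), SE = 8.43 × √(1 − R²). The documents give no R², so a range is assumed. At 0.10, for example, SE = 8.43 × √0.90 = 8.00 ml and power = Φ(2.626 − 1.645) = 83.7%.

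| Assumed R² | SE (ml) | Power, one-sided 0.05 | Power, two-sided 0.05 | Evaluable per arm for 80% (one-sided) |
|---|---|---|---|---|
| 0 | 8.43 | 80.1% | 70.2% | 172 |
| 0.02 | 8.35 | 80.8% | 71.1% | 168 |
| 0.05 | 8.22 | 81.9% | 72.4% | 163 |
| 0.10 | 8.00 | 83.7% | 74.7% | 155 |
| 0.20 | 7.54 | 87.3% | 79.5% | 138 |

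The two-sided column is shown because the analysis section gives a 0.05 threshold without saying how many sides.

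**4. What the formula leaves out.** Each covariate that was not balanced by design costs a little precision through chance correlation with arm. BMI as one term, T1 to T4a as three and N0 to N3 as three make seven, so the variance rises by roughly 7/344 = 2%. At R² = 0.02 the net gain is therefore about nil. Site and approach cost little here, because minimisation already keeps them nearly balanced.

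**The case against.** The strongest reply is that nothing here is wrong. An unadjusted comparison in a randomised trial is valid, the trial is sized for exactly that test, and it reaches its target. A condensed article often leaves covariate lists to an analysis plan, which is not shown. The validity argument stands in full and sets the limit of this point. The second argument stands in part: an analysis plan could add a model, but the article does name its tests, and they are unadjusted. The comment is on that stated choice.

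The evidence on predictors is also thin. Only obesity is tied to bleeding, and cautiously. Entry at BMI 25 or above narrows the range and may reduce what BMI explains. The planning SDs are almost as large as the means, which suggests a right-skewed outcome and makes a high R² on the millilitre scale hard to assume. This stands, and is why the range includes 0.02.

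Four stronger readings are tempting, and the document does not support them:

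- *Planned extent of gastrectomy is already recorded before allocation, so adjusting for it is free.* The article says what determines the resection range. It does not say that a planned extent is recorded before randomisation. For patients already enrolled it would have to be coded from gastroscopy reports.
- *Extent and stage are documented predictors of bleeding.* They are plausible, but no passage says so.
- *Chance imbalance biases the CTA effect.* The standard error already allows for chance imbalance. As an illustration, assume that 35% have total gastrectomy and that it bleeds 40 ml more. The SD of the between-arm difference in proportions is √(2 × 0.35 × 0.65/172) = 5.1 points, so a gap of 10 points or more arises in about 5% of trials. A 10-point gap would move the estimate by 4 ml, under half of one standard error.
- *The minimisation factors should be extended.* Recruitment was expected to end in November 2021 and the article appeared in December 2021, though Trial status says enrolment continues. Major design changes need a formal amendment and ethics approval. The change would reach few patients and is not needed if the analysis adjusts.

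**Conclusion.** The point holds as one of efficiency. The article commits blood loss and the other continuous outcomes to unadjusted tests, while BMI and clinical stage are available for every patient from eligibility. There is no bias, and the sample size is adequate on its own one-sided assumptions.

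The gain cannot be fixed from the document. One-sided power would go from 80.1% to about 81.9% at R² 0.05, 83.7% at 0.10 and 87.3% at 0.20; at 0.02 or below the gain is negligible. These figures rest on the planning means and SDs, 172 evaluable per arm, a normal approximation and an assumed R². The change is worth making because it needs almost no effort and the planned test is kept, not because a large gain can be promised.

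**What to change.** Before the data are unmasked, pre-specify the main blood-loss analysis as a linear model with arm, BMI as a continuous value, clinical T and N stage as recorded at eligibility, and the minimisation factors (site and surgical approach). Use robust standard errors, given the unequal SDs and likely skewness. Report the adjusted mean difference with its confidence interval, and keep the unadjusted test as a sensitivity analysis. The same covariates can be used for lymph node count, length of stay and cost. Stage must be the value fixed before allocation, so that the CTA examination cannot influence it.

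Lesion location from the pre-randomisation gastroscopy report may be added as a proxy for planned extent, provided that it can be coded blind to arm.

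Cost: analysis wording only for the core model, with no extra patients, procedures or data. The optional lesion-location covariate adds some coding work. The allocation scheme stays as it is.

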### Participant selection

Patients who are diagnosed with gastric cancer and plan to undergo laparoscopic or robotic gastrectomy will be enrolled from the 14 centres listed in Table 1. The launching conference was held online and was used to inform the participating staff about the details of the GISSG 20–01 trial. To obtain enough enrolled patients, all gastrointestinal surgeons in the participating centres were informed that the clinical trial was recruiting, and hospitalized patients were given the details about the trial for the purpose of enrolment. There are usually four ways to recruit patients: inpatients of gastrointestinal surgery, outpatients of gastrointestinal surgery, displaying poster at outpatient clinic or releasing recruitment information on the Internet. The enrolment of the first patient was started in November 2020, while it is anticipated that the deadline for the recruitment of the patients will be in November 2021. In the end, 382 patients who meet the inclusion criteria will be included in this trial. The study protocol and informed consent form were approved by the ethics review board of all research hospitals before the enrolment of any patients. Well-trained research doctors are responsible for introducing the main contents of the study to the patients and obtaining informed consent from patients who voluntarily participate in the trial in each centre. The flowchart that demonstrates the process of enrolment of the patients is shown in Fig. 1. The study protocol was revised to version 1.3 in December 2020. Any major modifications to the study protocol that may have a significant influence on the execution of the trial, including changes in the inclusion or exclusion criteria, number of samples or the study design, will require a formal amendment to the protocol. Such major modifications will be agreed up on by the GISSG (Gastrointestinal Surgery Study Group) and approved by the ethics review board. Protocol modifications are transmitted through the research meeting, and the electronic manual is distributed to the sub-centre researchers. An integral checklist of items in accordance with SPIRIT (Standardized Protocol Items: Recommendations for Intervention Trials) (2013 version) was supplied in additional file 1.

**Table 1 Tab1:** The 14 participating centres

Number	Centre	Department	Investigator
01	The Affiliated Hospital of Qingdao University	Gastrointestinal Surgery	[name]

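### OS and DFS are timed from surgery, which follows randomisation and CTA, so a randomised patient who is never operated on has no survival time

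*Protocol article*

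**What the plan says.** All places are in the protocol article.

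- **Time origin.** Data collection and analysis has OS and DFS "defined as the time from surgery to death and the time from surgery to tumour recurrence", with death from any cause also counting for DFS. Both "will be assessed by the Kaplan–Meier method with the log-rank test", and Cox models are added. No other section gives a different starting point.
- **Enrolment.** Under Participant selection, patients who "plan to undergo laparoscopic or robotic gastrectomy will be enrolled". Surgery is an intention at that stage.
- **Order of events.** Randomization describes central allocation that is open to investigators and patients. Interventions and CTA protocol then says that "the patients in the CTA group will be asked to undergo the CTA examination once they are randomly assigned to the experimental group". The operation comes after that.
- **Interval.** The Fig. 2 legend places the preoperative study time point "2 weeks before operation".
- **Follow-up.** The Follow-up section sets up its team for patients after surgery, and the dated visits in the Fig. 2 legend run from 1 to 36 months after surgery.
- **Status.** In the Abstract and in Outcomes, 3-year OS and DFS stand behind the primary endpoint, blood loss.

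**The concern.** The survival clock starts at an event that comes after randomisation and after the whole experimental intervention. In a trial that randomises at or after the operation, a surgery origin costs little. Here it decides who enters the comparison. A randomised patient who withdraws, deteriorates, dies or is otherwise not operated on has no time zero, so no OS or DFS value exists even if the death is recorded. Time between randomisation and surgery is also left out for everyone else.

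The multiple imputation planned in the same section does not repair this, because the survival time of such a patient is undefined rather than missing. At stake is whether the long-term comparison, which the Objective section names as an aim, is made between the groups as randomised or between those who reached theatre.

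**Working it through.** **1. The plan's own figure.** The article gives no sample size or event count for OS or DFS. Its one calculation is for blood loss, and it supplies the denominator used below. Inputs from Sample size computation: 72.5 ± 66.4 ml and 93.5 ± 88.4 ml, one-sided α = 0.05, power 80%, dropout about 10%.

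- Difference: 93.5 − 72.5 = 21.0 ml.
- SD: √((66.4² + 88.4²)/2) = √6111.76 = 78.18 ml.
- n per arm: 2 × (1.645 + 0.842)² × 78.18² / 21.0² ≈ 171.4, so 172.
- Total with dropout: 344 / 0.9 = 382.2, which matches the stated 382.

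This figure does not depend on the survival time origin, and nothing in this point changes it.

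**2. Order of events.** Enrolment with surgery planned, then randomisation, then CTA in one arm, then surgery, which is time zero for OS and DFS. A patient who leaves this sequence before the last step has no survival time under the stated definition.

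**3. How many patients.** The documents give no non-operation rate, so the range is assumed. Patients affected = rate × 382.

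| Assumed share never operated on | Patients without an OS or DFS time |
|---|---|
| 1% | 3.8, about 4 |
| 2% | 7.6, about 8 |
| 5% | 19.1, about 19 |
| 10% | 38.2, about 38 |

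**4. When this biases the comparison.** As an illustration only, assume 3-year OS of 75% in operated and 30% in non-operated patients, the same in both arms. With non-operated share f, survival as randomised is (1 − f) × 0.75 + f × 0.30. Among operated patients the arm difference is then zero. As randomised, it is 0.45 × the difference in f between the arms.

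| Non-operated share, one arm vs the other | Difference as randomised, missed by the operated-only analysis |
|---|---|
| 2% vs 2%, or 5% vs 5% | 0 |
| 2% vs 5% | 0.45 × 0.03 = 1.35 points |
| 5% vs 10% | 0.45 × 0.05 = 2.25 points |
| 0% vs 10% | 0.45 × 0.10 = 4.5 points |

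Equal non-operation gives no difference between arms. The last row is an extreme, not an expectation.

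**5. The time shift.** The article does not state the interval from randomisation to surgery. Taking the 2-week preoperative time point as a guide, the shift is 14 days in 36 months (about 1,096 days): 14 / 1,096 ≈ 1.3%.

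**The case against.** The strongest reply is that nothing in the article links CTA to whether or when a patient is operated on. Both arms have the same mandatory enhanced CT for staging, and clinical stage on CT is an inclusion criterion. For the quality of the CTA image describes CTA as showing arterial origins, branches and vessel type. A reader might infer that the extra imaging changes staging, operability or the operation date, but the documents give it none of these roles. This stands: a difference between arms is possible because allocation is open and patients may withdraw, but it is not shown.

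A reader might also take the 10% dropout in Sample size computation as the number not operated on. It is a ceiling for all causes, used to size the blood-loss comparison, and nothing ties it to non-operation. The 10% row above is therefore only the top of an assumed range. Some patients who withdraw before surgery would also have no survival follow-up under either origin.

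The exclusion of patients "whose tumour was found to be unresectable during the operation" may look like an example of the same problem. It is not. Those patients reached theatre and have a surgery date. They are lost through an exclusion applied after randomisation, which is a separate matter that a new time origin alone would not cure.

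Finally, timing from surgery is common in surgical trials, and these endpoints are secondary. Both facts limit the weight of the point. Neither gives a survival time to a randomised patient who has no operation.

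**Conclusion.** The point holds as a defect of definition that the article itself fixes. It is not a detail left to an unseen analysis plan. OS and DFS are undefined for randomised patients who are not operated on, and the arms are compared in a subset formed after randomisation.

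The number affected is unknown: about 4 to 38 of 382 for an assumed 1% to 10%. Bias between arms needs unequal non-operation or unequal intervals to surgery. The illustrative 1.35 to 4.5 points rest on assumed unequal rates and on assumed survival of 75% and 30%. It would go too far to say that the comparison has lost the protection of randomisation outright, since the documents neither quantify non-operation nor link it to arm. The effect is probably small. The primary endpoint and the sample size are untouched. The change is still worth making, because it removes the doubt at little cost.

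**What to change.** In Data collection and analysis:

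- Define OS as time from randomisation to death from any cause.
- Define DFS as time from randomisation to recurrence or death from any cause.
- Apply both to all randomised patients in their assigned arm.
- State how a patient without a resection counts for DFS, since such a patient was never free of disease and cannot recur. One option is an event at a fixed early time.
- Keep the surgery-origin analysis in operated patients as a sensitivity analysis.

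The cost is small but not nil. Central randomisation should already supply the randomisation date. For operated patients, visits to 36 months after surgery already cover 36 months from randomisation. What must be added is collection of vital status for the randomised patients not operated on, because Follow-up and the Fig. 2 legend schedule visits only after surgery. The article reports recruitment as ongoing, so this could be arranged by amendment, and the definitions should be fixed before survival data are analysed.
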